# Universal versus conditional three-day follow up visit for children with uncomplicated fever at the community level: design of a cluster-randomized, community-based, non-inferiority trial in Tanganyika, Democratic Republic of Congo

**DOI:** 10.1186/s12887-017-0792-1

**Published:** 2017-01-26

**Keywords:** Non-inferiority, Pediatrics, Uncomplicated fever, Integrated community case management, Community health worker, Cluster randomized trial, Democratic Republic of the Congo

## Abstract

**Background:**

The current recommendation within integrated Community Case Management guidelines that all children presenting with uncomplicated fever and no danger signs be followed up after three days may not be necessary. Such fevers often resolve rapidly (usually within 48–96 h), and previous studies suggest that expectant home care for uncomplicated fever can be safely recommended. We aim to determine the non-inferiority of a conditional versus a universal follow-up visit for these children.

**Methods:**

We are conducting a cluster-randomized, community-based, non-inferiority trial enrolling ~4300 children (ages 2–59 months) presenting to community health workers (CHWs) with uncomplicated fever in Tanganyika Province, Democratic Republic of the Congo. Clusters (*n* = 28) of CHWs are randomized to advise caretakers of such children to either 1) return for a follow-up visit on Day 3 following the initial consultation (Day 1), regardless of illness resolution (as per current guidelines) or 2) return for a follow-up visit on Day 3 only if the child’s signs have not resolved. Enrolled children are followed up at Day 7 for a repeat assessment and recording of the primary outcome of the study, “failure”, which is defined as having fever, diarrhea, pneumonia or decline of health status (e.g. hospitalization, presenting danger signs, or death).

**Discussion:**

The results of this trial will be interpreted in conjunction with a similarly designed trial currently ongoing in Ethiopia. If a follow-up visit conditional on continued illness is shown to be non-inferior to current guidelines stipulating universal follow-up, appropriate updating of such guidelines could reduce time and human resource pressures on both providers and caregivers throughout communities of sub-Saharan Africa and South Asia.

**Trial registration:**

This trial was registered at ClinicalTrials.gov (NCT02595827) on November 2nd, 2015

## Background

In settings burdened with elevated under-five morbidity and mortality, and challenged by limited access to health care services, community health workers (CHWs) often provide first-level care for sick children aged 2–59 months directly in the community through the implementation of integrated community case management (iCCM) of common childhood illnesses. Current World Health Organization (WHO) iCCM guidelines prescribe that a febrile child presenting to a CHW be assessed for malaria, pneumonia, and diarrhea, and for general danger signs (e.g. child is unable to drink or breast feed, is vomiting everything, is having convulsions, is lethargic or unconscious, and/or has chest in-drawing). CHWs provide direct treatment for confirmed malaria, diarrhea, and pneumonia, and, if any danger sign is present, refer the child immediately to a health center for more extensive care. However, when a febrile child has none of the aforementioned illnesses or danger signs, the CHW provides the child with an antipyretic and *advises the caregiver to return to the CHW for a follow-up consultation on Day 3* [1].

Such uncomplicated childhood febrile illnesses are common, are often due to viruses, and in many cases resolve rapidly and spontaneously (i.e. often within 48 h, and almost always within 96 h) [2–5]. In a study of 986 mRDT-negative children at rural health facilities in coastal Tanzania randomized to receive or not receive anti-malarials only 24 (2.4%) developed malaria; investigators identified only 3 cases of bacteremia and 1 case of urinary infection, along with 238 viral pathogens in stool and/or nasopharyngeal swabs [6]. There were no severe adverse events related to untreated illness, and no deaths. Among 1000 children presenting with fever at outpatient clinics in another study in both urban and rural mainland Tanzania, 71% had viral infections, and in most children the fever was self-limiting [7]. A randomized controlled cross-over study in Tanzania supported the safety of withholding artemisinin-based combination therapy (ACT) to mRDT negative patients receiving care in the community [8] and a study in Zambia found that only 8.2% of mRDT-negative children treated in the community with an antipyretic alone continued to have fever or were reported by the caregiver to be unwell at the time of the follow-up visit (day 5–7) [9]. These results suggest that in cases of febrile illness among children without danger signs, and with no other obvious cause of fever, expectant management at home can be safely used without a follow-up visit to the CHW on Day 3.

Therefore, current guidelines instructing CHWs to universally advise caregivers of children with uncomplicated fever to return on Day 3, even in the absence of continued fever or other signs, may be unwarranted and may create a substantial additional burden on CHW and caregiver time and resources. The extensive iCCM package that is delivered by CHWs, who are often volunteers, leads to a substantial workload and opportunity costs (i.e. limited time available to spend on income-generating activities). Caregivers often have to travel long distances by foot to reach a CHW, preventing them from engaging in income-generating activities as well.

One possible change to the current guidelines would have the child’s caretaker advised to return with the child for reassessment only in instances where signs persist or worsen. In order to provide the evidence base for such an update to global iCCM guidelines, we have designed a cluster-randomized, community-based trial to examine the non-inferiority of reassessment of RDT-negative febrile children without danger signs only in cases where signs do not resolve, compared with universal follow-up (independent of sign resolution), as recommended by WHO.

## Methods

### Aims

The primary aim of this study is to determine if the likelihood of clinical deterioration (“failure”) among children between 2–59 months of age in Tanganyika Province, DRC that present with an uncomplicated fever to CHWs is similar between those advised universally to be followed up on Day 3 and those advised for follow up only if illness does not resolve. At seven days post-enrollment, children are considered as “failed” if they present with persistent fever, persistent illness, or decline of health status (e.g. hospitalization, presenting danger signs, or death). We hypothesize that the proportion of children that meet this primary outcome determination under current guidelines (“universal”) is 5% and that the true rate of failure in the condition under study (“conditional”) is 6%. The null hypothesis is that the conditional follow-up approach is inferior and that children in this group will yield a failure rate at least 4% higher than that of the universal follow-up group. Conditional follow-up will be considered non-inferior to universal follow up if the upper bound of a one-sided 95% confidence interval around the absolute difference in outcome rate (conditional follow up minus universal follow up) does not exceed 4%.

Secondary aims of the study include describing the clinical presentation, care-seeking patterns, and outcomes among children that are classified as “failed” at Day 7, estimating the frequency of scheduled and spontaneous visits among all children, hospitalization and death rates among all children, and longer-term outcomes (based on data collected during Day 14 and Day 28 house visits) of children that were classified as “failed” at Day 7. In addition, a qualitative portion of the study with a limited sample size will look at CHWs’ and caretakers’ perceptions of the conditional vs. universal follow-up message.

Enrollment for this study was initiated in October 2015 and will be completed by the end of 2016. The study is a collaboration between the International Rescue Committee (IRC) and the Johns Hopkins Bloomberg School of Public Health.

### Study site and population

This study is implemented in Tanganyika Province in the southeastern DRC. With a density of 18 inhabitants per square kilometer, Tanganyika has endemic malaria transmission and low access to health care services due to geographic barriers and a lack of financial resources of those seeking care. To address these barriers, the International Rescue Committee (IRC), with Ministry of Public Health oversight, is currently implementing the Canadian International Development Agency-funded and WHO-administered Rapid Access Expansion (RAcE) program, a 4-year effort to train and deploy CHWs to deliver iCCM across six countries, including in 11 health zones in Tanganyika Province. Burden of fever in this setting is high: 2014 RaCE program data indicate that CHWs in seven of the health zones evaluated a total of 79,000 cases of fever in children under five, 13,000 of whom were mRDT negative.

The non-inferiority trial is being conducted in two RaCE-participating health zones with a total under-five population of ~168,000 (Kalemie and Nyemba, under-five populations of 94,000 and 74,000, respectively). Within each zone, 14 health areas are included, each having both a health center, and a team of associated CHWs (total 258; approximately 5–10 per area; average 104 (±81) children per CHW) who work within that particular health area. The CHWs are men and women with at least primary school education level, who are literate and locally resident, elected by the community, and have received five days of training on the iCCM algorithm as per DRC Ministry of Public Health guidelines. Medications (e.g. ACT, amoxicillin, oral rehydration solution (ORS), zinc, paracetamol, and ACT suppository for severe malaria cases requiring referral) and supplies are distributed to CHWs on a monthly basis, and the care they provide to children in their community is free of charge.

### Randomization

The unit of randomization in this trial is the health area (*n* = 28), and CHWs working within a particular health area are thus allocated to the same group (either “universal” or “conditional” follow-up advice given to caretakers of eligible children); all children enrolled by CHWs within a health area constitute the study cluster. Allocation to the “universal” versus “conditional” arm was done via restricted randomization whereby units were balanced on zone and health area estimates of 1) population size, 2) prior 6-month likelihood of mRDT-negative febrile children (number of children mRDT negative/under-five population), and 3) geographic distance from CHW to zonal health center. Of all possible randomization sequences (*n* = ~40.1 million, generated using STATA version 13.1), 43,504 sequences were balanced on zone ***and*** had ratios of the above three indicators between 1/1.05 and 1.05. After confirming the validity of the restriction procedure (approximately equal probability of any two units being assigned to the same or different arms), one of these sequences in the restricted subset was selected at random. It was not possible to mask the clustered allocation from participants, CHWs, or data collectors).

### Sample size

To calculate sample size, we set the outcome rate in the “universal” follow-up group to 5%, and assumed that the (true) corresponding outcome rate in the “conditional” follow up group is no more than 6%. For the purposes of concluding that the “conditional” follow up is non-inferior to the “universal” follow up approach, using the simple approach outlined by Blackwelder [10] and extending the methods of Hayes and Bennett [11], we first estimated the coefficient of variation (k) of the true failure rate across our available health areas; we conservatively estimated that k is 0.35, implying that the true cluster-specific failure rates vary between 1.5 and 8.5% (i.e. 5%*(1 ± 2 k)). Next, utilizing data from the first six months of 2015, aggregated from monthly reports from CHWs working in Kalemie and Nyemba health zones, we anticipated that approximately 493 negative mRDT cases would occur per month over 28 health areas. We estimated that about 70% of these mRDT negative cases would be eligible (i.e. excluding those cases with danger signs or other CHW treatable conditions [pneumonia, diarrhea]). Given the above assumptions, and desiring 12 complete months of enrollment, the estimated average cluster size over that anticipated timeframe is equal to (70%*493*12)/28 = 148. Assuming that about 10% of the eligible children will not participate or will be lost to follow up (reducing this yield to 148*.09 = 133, the total number of health areas required to detect (with 80% power) non-inferiority of the “conditional” follow up approach given the above parameters was 24, (12 per group). Rather than exclude just 4 of our available 28 health areas, we decided to include all 28, increasing the number of clusters to 14 per group (this increased our estimated power to 86.8%), and leading to an initial estimated final enrollment of 3730 children. After approximately 6 months of actual study enrollment, however, our actual observed per-cluster yield had increased to 152, leading to a revised estimate of the total enrollment; by the completion of the enrollment period, we will enroll approximately 4270, or 2135 children per group.

### Eligibility and intervention

All CHWs were trained on the study protocol including the appropriate follow up message for children with uncomplicated fever depending on study arm allocation, and the eligibility criteria for study inclusion. CHWs identify eligible children while conducting routine iCCM services in their communities. Assessment of children presenting for care under iCCM guidelines includes examining the child, asking the caregiver about signs of illness (e.g. danger signs, diarrhea, fever, cough, screening the child for malnutrition by measuring the mid-upper arm circumference [MUAC] of the child), and (rapid) testing for malaria. Some reported signs (such as cough or difficulty breathing) will prompt the CHW to look for chest in-drawing and measure respiratory rate. Children ***ineligible*** for this study are those the CHW determines to have one or more danger signs and/or malaria, pneumonia, or diarrhea; those with danger signs are immediately referred to the nearest health centers, while the others are treated and advised to return on Day 3. The remaining febrile children (i.e. those with neither danger signs nor a CHW-treatable illness) are eligible for enrollment. Such eligible children are provided an antipyretic and caretakers are advised if signs should worsen in the coming days, they should immediately seek care at the health center. Finally, the CHW provides study-arm specific advice about when to return for a follow up visit:In the “universal” study arm, CHWs advise all caregivers to come back with the child on Day 3.In the “conditional” (intervention) study arm, CHWs advise caregivers to come back with the child on Day 3 only if signs remain the same, or worsen. Caregivers are told that if they determine that the child is in good health, they do not need to return.

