### Quality control and supervision

In order to ensure that all eligible children are correctly identified, data collectors check the registers of CHWs in the health area where they work on a weekly basis.

Quarterly meetings are organized for all data collectors and research support staff to provide feedback based on the data collected, to address challenges experienced by the data collectors in the field and to identify best practices. In addition, each data collector receives a quarterly individual supervision visit in the health area where (s)he works. During this visit, the Research Manager accompanies the data collector on a Day 7 visit to observe and evaluate the data collector while at work and to provide coaching and feedback in order to strengthen the data collector’s capacities. In addition, the Research Manager conducts spot checks of CHW registers working in the data collector’s health area during the individual supervision visit to ensure that all eligible children are identified by the CHWs and data collectors.

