### Analysis

All children enrolled and providing available data from the follow-up visit on Day 7 will be included in the analysis. First, we will present descriptive information on the recruitment, enrollment, and follow up of children with uncomplicated fever using a participant flowchart (Fig. 1). We will then assess characteristics of enrolled children to determine the extent to which our randomization procedure at the health area level achieved balance across the study arms; these characteristics will include infant, maternal/paternal, household, and socio-economic variables. Variables that are imbalanced will be noted for possible inclusion in a subsequent adjusted analysis.

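### Unmasked CHWs decide eligibility after allocation, and that label alters the Day 3 advice only in the conditional arm; the stated checks and analysis are not built to detect differential classification

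*Protocol article*

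**What the plan says.** All places are in the Methods of the Protocol article.

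- **Randomization.** Health areas were allocated as whole clusters, and "It was not possible to mask the clustered allocation from participants, CHWs, or data collectors".
- **Eligibility and intervention.** "CHWs identify eligible children while conducting routine iCCM services in their communities". The ineligible "are those the CHW determines to have one or more danger signs and/or malaria, pneumonia, or diarrhea"; of these, "those with danger signs are immediately referred to the nearest health centers, while the others are treated and advised to return on Day 3". For eligible children in the universal arm, "CHWs advise all caregivers to come back with the child on Day 3". In the conditional arm the caregiver is asked back on Day 3 only if the child is no better or is worse.
- **Consent and enrollment.** In both arms the eligible label leads the CHW to notify the data collector, and a home visit follows on Day 7. Initial-visit data for enrolled children are taken from the CHW's iCCM records, which is also used to confirm the eligibility assessment.
- **Quality control and supervision.** "data collectors check the registers of CHWs in the health area where they work on a weekly basis", and the Research Manager spot-checks registers at quarterly supervision visits.
- **Analysis.** Enrolled children are compared by arm; "these characteristics will include infant, maternal/paternal, household, and socio-economic variables". Adjusted analyses follow if an imbalance has been noted.
- **Sample size.** "We estimated that about 70% of these mRDT negative cases would be eligible".

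**The concern.** Randomizing health areas makes the populations comparable. It does not protect the case mix of children whom unmasked staff select afterwards. Here the Day 3 consequence of the selection differs by arm. In the universal arm, recording pneumonia or diarrhea leaves the Day 3 advice unchanged. In the conditional arm it turns a conditional return into a fixed one. A CHW uneasy about a borderline child there has a reason to record a treatable illness, and that child leaves the trial. The reverse is also possible: a borderline child may be classed as uncomplicated because no routine return is then needed.

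The first drift would lower the conditional arm's failure rate for reasons unrelated to the follow-up policy and make the 4-point rule easier to pass. The second would raise that rate and cost power. According to the Discussion, a non-inferior result could support simpler guidelines, so the first is the more consequential error.

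**Working it through.** **1. Day 3 advice by label and arm (Eligibility and intervention)**

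| CHW's label on Day 1 | Universal arm | Conditional arm |
|---|---|---|
| Treatable illness, no danger sign | return Day 3 | return Day 3 |
| Uncomplicated fever (eligible) | return Day 3 | return Day 3 only if not improved |
| Danger sign | referred at once | referred at once |

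Only the conditional column changes between the first two rows. Treatment and the Day 7 visit also depend on the label, but in the same way in both arms.

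**2. The plan's own figures**

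Inputs from Sample size: p0 = 0.05, p1 = 0.06, k = 0.35, 133 children per cluster; margin 0.04 and one-sided 5% from Aims. The Hayes-Bennett form with a non-inferiority shift gives

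c = 1 + (1.645 + 0.842)² × [p0(1−p0)/m + p1(1−p1)/m + k²(p0² + p1²)] / (0.04 − 0.01)²

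The bracket is 0.000357 + 0.000424 + 0.000747 = 0.001528, so c = 11.50, or 12 per group and 24 in all, as stated. With 14 per group, SE = √(0.001528/13) = 0.01084 and power = Φ(0.03/0.01084 − 1.645) = 86.9%, against 86.8% stated. The calculation takes it that both arms enrol comparable children.

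**3. Illustration of differential classification (f and r are assumptions)**

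Set true failure at the margin, 9% conditional against 5% universal. Let a share f of otherwise eligible conditional-arm children, with failure risk r, be classed as ineligible. Then

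observed conditional rate = (0.09 − f·r)/(1 − f).

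With the observed yield of 152 per cluster, k = 0.35 and 14 clusters per arm:

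SE = √[(0.0475/152 + 0.0819/152 + 0.1225 × 0.0106)/14] = √(0.002150/14) = 0.0124.

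False non-inferiority = Φ(−1.645 + shift/SE).

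| f | r | Observed conditional rate | Shift (points) | False non-inferiority | Eligible share, 70% × (1−f) |
|---|---|---|---|---|---|
| 0 | – | 9.00% | 0 | 5.0% | 70.0% |
| 3% | 18% | 8.72% | 0.28 | 7.8% | 67.9% |
| 5% | 25% | 8.16% | 0.84 | 16.7% | 66.5% |

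Dividing by 13 instead of 14, as in step 2, gives SE 0.0129 and 7.7% and 16.1%.

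**4. Would a tally of eligible shares reveal this by itself?**

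Expected mRDT-negative children per cluster: 493 × 12/28 = 211. With an assumed between-cluster SD of 5 points in the eligible share, the SE of the arm difference is √[2 × (0.7 × 0.3/211 + 0.05²)/14] = 0.0223. The differences implied above are 70 − 67.9 = 2.1 and 70 − 66.5 = 3.5 points. Power of a two-sided 5% test is Φ(0.021/0.0223 − 1.96) = 15% and Φ(0.035/0.0223 − 1.96) = 35%. A tally is informative but too weak to act as a test.

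**The case against.** The strongest case against runs as follows.

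- **The label does more than set Day 3 advice.** A reader might infer that it alters a child's care in the conditional arm alone. The document does not support that: treatment and the Day 7 visit depend on the label in both arms. The asymmetry concerns the Day 3 advice for children without danger signs.
- **The registers are not blind to the problem.** A reader might infer that the checks can never show it. They can find eligible children who were missed and labels that conflict with recorded signs. What they are not designed for is a between-arm difference in how signs were judged or written down.
- **The motive is modest and the room for judgement limited.** A worried CHW could simply ask the caregiver to return, and the plan has a sub-analysis restricted to children for whom per-protocol advice was reported. Malaria rests on a rapid test and pneumonia on a counted respiratory rate. This makes large drift less likely, but classification still depends on caregiver report and the CHW's own examination.
- **Detail may sit elsewhere.** The baseline variables are named as categories, a stratification by days of fever is specified, and a recruitment flowchart is planned whose figure is not shown. The absence of a covariate list is therefore no finding. What the article does state, adjustment only when imbalance is noticed among enrolled children, is a weaker method than one fixed in advance.
- **The size is assumed.** That is correct, and it is why the figures are offered only as illustration.

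**Conclusion.** The concern holds as a design weakness and not as a demonstrated bias. Unmasked CHWs set the case mix after allocation, the Day 3 consequence of their label exists in one arm only, and neither the record checks nor the imbalance-triggered adjustment is aimed at it.

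The rise in false non-inferiority from 5% to about 8 to 17% rests on four things: true rates exactly at the margin, k = 0.35, drift in one direction, and assumed values for the share lost (3 to 5%) and its failure risk (18 to 25%). The document supplies neither of the last two. A reader might infer that the trial is biased towards non-inferiority; the document does not support that, since the opposite drift is equally open and there is no evidence of either. The change is worth making because it draws on records already being handled.

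**What to change.** 1. From the registers already checked weekly, report by arm and health area the number of mRDT-negative febrile children, the share classed as eligible, and exclusions by reason. Present this as a descriptive cluster-level comparison with a confidence interval. Do not use it as a pass/fail trigger or as a test against the 70% planning value.
2. Replace adjustment only when imbalance is noted with a pre-specified, cluster-aware adjusted risk difference that is always reported. Use Day 1 features extracted from the iCCM record, such as age, days of fever, cough and MUAC.
3. State in advance that a non-inferiority conclusion will be reported with qualification if the adjusted upper bound reaches 0.04.

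The cost is somewhat more abstraction during existing checks and one model, with no extra visits or children. The limit should be stated too: covariates recorded by the same unmasked CHW can only partly correct selection made by that CHW, and the conclusion may have to carry a qualification.
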